# Implementing the theory-based advance care planning ACP+ programme for nursing homes: study protocol for a cluster randomised controlled trial and process evaluation

**DOI:** 10.1186/s12904-019-0505-7

**Published:** 2020-01-08

**Keywords:** Advance care planning, Complex intervention, Nursing home, Process evaluation, Effectiveness, Care staff, Educational intervention, Implementation

## Abstract

**Background:**

Research has highlighted the need for improving the implementation of advance care planning (ACP) in nursing homes. We developed a theory-based multicomponent ACP intervention (the ACP+ programme) aimed at supporting nursing home staff with the implementation of ACP into routine nursing home care. We describe here the protocol of a cluster randomised controlled trial (RCT) that aims to evaluate the effects of ACP+ on nursing home staff and volunteer level outcomes and its underlying processes of change.

**Methods:**

We will conduct a cluster RCT in Flanders, Belgium. Fourteen eligible nursing homes will be pair-matched and one from each pair will be randomised to either continue care and education as usual or to receive the ACP+ programme (a multicomponent programme which is delivered stepwise over an eight-month period with the help of an external trainer). Primary outcomes are: nursing home care staff’s knowledge of, and self-efficacy regarding ACP. Secondary outcomes are: 1) nursing home care staff’s attitudes towards ACP and ACP practices; 2) support staff’s and volunteer’s ACP practices and 3) support staff’s and volunteers’ self-efficacy. Measurements will be performed at baseline and eight months post-measurement, using structured self-reported questionnaires. A process evaluation will accompany the outcome evaluation in the intervention group, with measurements throughout and post-intervention to assess implementation, mechanisms of impact and context and will be carried out using a mixed-methods design.

**Discussion:**

There is little high-quality evidence regarding the effectiveness and underlying processes of change of ACP in nursing homes. This combined outcome and process evaluation of the ACP+ programme aims to contribute to building the necessary evidence to improve ACP and its uptake for nursing home residents and their family.

**Trial registration:**

The study is registered at ClinicalTrials.gov (no. NCT03521206). Registration date: May 10, 2018. Inclusion of nursing homes started March, 2018. Hence, the trial was retrospectively registered but before end of data collection and analyses.

## Background

Timely advance care planning (ACP) is advocated as an important part of routine nursing home practice. A recent consensus definition defined ACP as a process that supports adults at any age or stage of health in understanding and sharing their personal values, life goals and preferences regarding future (medical) care, including end-of-life care [1]. If a person wishes, the contents of such conversations can be recorded in the form of an advance directive (AD) and may include choosing a durable power of attorney or proxy decision-maker [1, 2].

A number of previous studies in nursing home populations have shown that, if ACP is actually conducted, it can effectively decrease hospitalisation rates and hospital deaths, decrease overall health costs and increase treatment concordant with people’s wishes [3]. However, these findings usually do not come from studies using high-quality methodologies, as was identified in a recent systematic review using GRADE (Grading of Recommendations Assessment, Development, and Evaluation) criteria to assess the quality of the studies that had evaluated effects of ACP in nursing homes. In addition, very few randomised controlled trials (RCT) in this area have been published [3]. Moreover, the uptake of ACP in clinical practice remains limited and nursing home residents’ wishes about their preferred medical treatment and care are often not, or not in time, explored [4–6]. Previous epidemiological studies have shown that uptake is also low in Belgium where only half of deceased nursing home residents had documented wishes or preferences [7] and 38% of residents never engaged in ACP during their two-year stay in a nursing home [6].

Healthcare professionals’ lack of knowledge about ACP and their confidence in conducting ACP, are identified in the literature as prominent factors preventing them from engaging in ACP [8]. Improving this should be a first priority, given that two theoretical frameworks that describe successful ACP specify that sufficient knowledge and self-efficacy are necessary intermediate steps on the pathway to changing outcomes on the patient and family level [9, 10]. To improve the uptake of ACP in regular nursing home practice, we have developed the ACP+ programme for nursing homes in Flanders (Belgium). ACP+ is a theory-based multicomponent intervention focused on helping staff deliver ACP as part of routine nursing home care, implemented in a stepwise manner over the course of eight months with the help of an external trainer. The underlying theoretical model can be found elsewhere [10]. However, the effectiveness of ACP+ and its theoretical assumptions have not yet been tested using a high-quality research design. This article describes the study protocol of a cluster RCT with an embedded process evaluation. The study aims to evaluate the effects of ACP+ on nursing home staff and volunteer level outcomes and its underlying processes of change. The protocol is outlined according to SPIRIT (Standard Protocol Items: Recommendations for Interventional Trials) guidelines [11].

## Methods

### Trial design

We will perform a cluster randomised controlled trial (RCT) with embedded process evaluation. It is a superiority trial because it aims to establish whether the intervention is superior to usual practice in effectiveness [12]. The trial will be structured according to a nested cohort pretest-posttest design with a priori matching of clusters [13–15]. Clusters are nursing homes found eligible and willing to participate, which will be matched into pairs (1:1) by (in order) location (province in Flanders, type of facility (public, private non-profit or private for-profit) and number of beds. One of each pair will randomly be assigned to either intervention or control group. A cluster RCT is recommended for this type of study because most intervention components target the entire nursing home. Randomising staff within facilities was not an option as it would have been impossible to prevent contamination among staff on the same wards [16]. Fig. 1 shows the flowchart of the RCT. Immediately after randomisation, baseline outcomes measures are performed (T0) and eight months later, outcome measurements (T1).

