
#### Blinding (masking)

The nature of the intervention makes it impossible to blind study participants because all those in the intervention group will receive additional training or information. During data collection, the researchers cannot be blinded because they will observe training sessions and conduct interviews with staff as part of the process evaluation, hence will know the staff who work in intervention facilities. The process evaluation will only be conducted in intervention facilities. During data analysis, researchers and statistician will be blinded for the unit of randomisation of each nursing home, using encrypted data.

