### Data collection, management and analysis

#### Data collection methods

In each facility, a key contact person (facility manager, head of care, head nurse or quality coordinator) will be identified. After randomisation, this key contact person will fill in the questionnaire concerning the baseline structural facility-level characteristics. In addition, the contact person lists *all* eligible nursing home staff and volunteers. Each eligible staff member/volunteer will be assigned an anonymous code, which will enable the research team to link T0 to T1 data. As part of baseline and post-assessment, they receive a structured self-report questionnaire with his/her personal code. They will put the questionnaire in sealed envelopes and deposit it in a locked letter box (only accessible to the researchers) in a central spot in the nursing home. As was done in a previous Flemish and EU study, two reminders will be sent [19, 32]. Using the anonymous codes, the researchers will register response. For non-responders, the contact person of the nursing homes will be asked to re-distribute the questionnaire to this professional and send out a general reminder. These procedures are repeated eight months after baseline measurement. Newly hired staff and new volunteers are added to the list of codes and will also receive a questionnaire.

Data collection procedures for the process evaluation, described in detail in Table 3, are the following:

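### Staff are listed and baseline questionnaires completed after randomisation, with no stated withholding of allocation, so a shift in T0 answers would enter the primary change contrast; the direction is unknown

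*Protocol article*

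**What the plan says.** **Order of events.** Under Trial design: "Immediately after randomisation, baseline outcomes measures are performed (T0) and eight months later, outcome measurements (T1". Data collection methods gives the same order for the facility data: "After randomisation, this key contact person will fill in the questionnaire concerning the baseline structural facility-level characteristics". The sentence that follows adds the respondents: "In addition, the contact person lists *all* eligible nursing home staff and volunteers". The contact is a facility manager, head of care, head nurse or quality coordinator, and is also asked to hand the questionnaire again to those who have not replied.

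**Masking.** The section on blinding says of participants: "The nature of the intervention makes it impossible to blind study participants because all those in the intervention group will receive additional training or information". On the research team: "During data collection, the researchers cannot be blinded because they will observe training sessions and conduct interviews with staff". Only the data analysis is blinded. No section says that homes or staff learn their allocation only after T0 has been returned.

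**Effect measure.** Outcome analysis defines the effect as the group-by-time interaction, that is, the difference between arms in mean change from T0 to T1, tested two-sided at 0.025.

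**Who belongs to the cohort.** Trial design says: "The trial will be structured according to a nested cohort pretest-posttest design". For the T1 round, Data collection methods says: "Newly hired staff and new volunteers are added to the list of codes and will also receive a questionnaire".

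**The concern.** T0 is half of a change contrast. If staff or their managers know the arm when T0 is completed, answers can move before any training has taken place, and the move is carried into the estimated effect with its sign reversed.

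The two primary outcomes are not equally exposed. Self-efficacy is a subjective rating over 12 items; someone who knows that training is coming may rate their own confidence lower (aware of a gap) or higher (motivated). Knowledge is an 11-item true/false test with uncertain answers scored as wrong. Effort can move it, but it leaves less room for re-rating.

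Sample size plans for only 70% initial response, and non-responders are followed up partly through the on-site contact. Who replies at T0 could therefore also differ by arm.

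The order is avoidable. According to Recruitment, agreement forms are signed before randomisation; according to Randomisation, all homes are identified before matching. The reason given for not blinding participants is that the intervention arm receives training or information. That has not yet happened at T0, so it does not explain why T0 follows allocation.

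**Working it through.** No figure in the article measures this bias. The calculation below only shows scale.

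**1. The plan's own figure.** Inputs from Sample size: mean cluster size 30, coefficient of variation 0.17, ICC 0.036, 161 staff per group, effect 0.5 SD, significance level 2.5%.

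- Design effect = 1 + ((0.17² + 1) × 30 − 1) × 0.036 = 2.075 (stated 2.07).
- Effective n per group = 161 / 2.07 = 77.8.
- Two-sided power for 0.5 SD at 0.025: 0.810 by normal approximation, and 0.8026 by noncentral t with 2 × 77.8 − 2 = 153.6 df. The stated 80.27% is reproduced.

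**2. How a T0 shift enters.** Effect = (T1 − T0, intervention) − (T1 − T0, control). If knowing the allocation moves intervention T0 by δ and leaves T1 unchanged, the expected estimate is the true effect − δ. A δ of −0.1 SD adds 0.1 SD to the estimate, and +0.1 SD removes it. Either is 0.1 / 0.5 = 20% of the target effect.

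**3. Standard error.** T1-only contrast: √(2 / 77.8) = 0.160 SD. Change contrast: 0.160 × √(2(1 − ρ)), where ρ is the T0-T1 correlation. The article gives no ρ, so 0.3 to 0.7 is assumed, with the same design effect for change.

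**4. Consequence of a 0.1 SD shift** (assumed; critical value 2.241):

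| ρ | SE of change (SD) | Rejection rate under no effect, shift favouring intervention | Power for 0.5 SD, no shift | Power for 0.5 SD, shift against intervention |
|---|---|---|---|---|
| 0.3 | 0.190 | 0.046 | 0.653 | 0.447 |
| 0.5 | 0.160 | 0.055 | 0.810 | 0.600 |
| 0.7 | 0.124 | 0.077 | 0.963 | 0.836 |

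At ρ = 0.5: 0.1 / 0.160 = 0.62, and Φ(−2.241 + 0.62) + Φ(−2.241 − 0.62) = 0.055. For power, Φ(0.4 / 0.160 − 2.241) = 0.60.

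Spreading the 161 over seven homes instead gives 23 per home, a design effect of 1 + (1.0289 × 23 − 1) × 0.036 = 1.816, and an SE of √(2 × 1.816 / 161) = 0.150. The rejection rate is then about 6% by normal approximation, or 4.7% with t on 6 df.

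**5. Differential T0 response.** Assume 60% response in one arm against 70% in the other, and a correlation c between propensity to respond and score. The mean among responders at response rate r is shifted by c·φ(z)/r, where z is the normal quantile at 1 − r. With c = 0.2 this is 0.129 against 0.099, a difference of about 0.03 SD. With c = 0.5 it is 0.322 against 0.248, about 0.07 SD. For 80% against 70% the differences are of similar size with opposite sign. These are shifts in the T0 mean of responders, not in the effect estimate: among staff measured twice, a stable difference in level largely cancels in the change.

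**The case against.** **Unblinded at T0 is an inference.** The article never says that staff are told their arm before T0, which follows randomisation at once. This stands: bias is possible, and a reader who concludes that it is built into the baseline goes beyond the text. But no withholding is described either, and the programme runs eight months, as long as the T0-T1 interval, so no protected baseline window is apparent.

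**Selection at listing is limited.** All eligible staff are to be listed, on criteria that leave little discretion. Researchers register response by code, and questionnaires go in sealed envelopes into a locked box. This stands as well: the text does not support a reading that managers choose favourable respondents. These safeguards do not prevent a respondent from answering differently.

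**The direction is open.** One might infer that a T0 difference would pass for a programme effect. That needs knowledge of the allocation to lower intervention scores or raise control scores at T0; the reverse hides an effect.

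**Already acknowledged.** The Discussion concedes that unblinded staff may answer differently and that some people will answer only at T1. It does not mention that listing and T0 follow allocation, which is the avoidable part.

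**New hires.** One might infer that they enter the primary analysis and dilute the effect, for example 0.9 × 0.50 = 0.45 SD if 10% of T1 respondents were wholly unexposed. The article says only that they receive a questionnaire, and the analysis set may be fixed in an analysis plan that is not shown. They may also be exposed during months 5 to 8, and any dilution would be conservative. This is a secondary point.

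**Conclusion.** The point holds in a limited form. Listing and T0 follow randomisation with no stated withholding of allocation, and the primary contrast subtracts T0, so an allocation-aware shift in T0 answers would pass straight into the estimate. Self-efficacy is the outcome mainly at risk. Differential response is possible but weaker.

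The size cannot be estimated from the article. Under an assumed 0.1 SD shift, the nominal 2.5% test rejects at about 5% to 8% under no effect (ρ from 0.3 to 0.7) if the shift favours the intervention. If it runs the other way, power at ρ = 0.5 drops from about 0.81 to 0.60. This rests on an unsourced shift, an assumed ρ, the same design effect for change, and a shift present at T0 but not at T1; an equal shift at both times would cancel. Blinded analysis does not correct it.

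**What to change.** **If T0 is not yet collected.** After the agreement forms are signed, close the coded staff list and collect T0 in all 14 homes, and only then run or disclose the randomisation. The instruments, codes and reminders stay as planned. The cost is a few weeks between agreement and start, during which some listed staff may leave.

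**If T0 is already collected.** This is plausible, since inclusion of homes began in March 2018 and the article appeared in January 2020. Report by arm the number listed, T0 response and T0 scores, and add a sensitivity analysis that compares the arms on T1 scores without using T0. Its SE (0.160 SD on the inputs above) equals that of the change contrast at ρ = 0.5 and is larger only when ρ exceeds 0.5. It removes the T0 problem but not unblinded answering at T1.

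**Secondary.** State that the primary analysis is based on staff on the T0 list, in line with the nested cohort design, and put people who answer only at T1 in a sensitivity analysis. This needs no extra data.

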**Fig. 1 Fig1:**
[figure not shown]
Flow diagram of ACP+ trial. ACP advance care planning; T0 baseline assessment; T1 post-assessment. The yellow blocks indicate the process evaluation data collection methods. The green indicates the intervention group

The outcome evaluation of the cluster RCT will be accompanied by an embedded process evaluation to evaluate processes of change (i.e. the implementation, mechanisms of impact and context) behind ACP in nursing homes. The design of the process evaluation is informed by the Medical Research Council (MRC) framework for process evaluations of complex interventions by Moore et al. [17] and a previously constructed theory of change [10]. The process evaluation has a mixed-methods design, collecting data throughout implementation of the intervention and post-intervention via structured diaries, notes, attendance lists, observation, post-training surveys and semi-structured interviews and focus groups. The study is registered at ClinicalTrials.gov (no. NCT03521206).

### Participants, intervention and outcomes

#### Setting

The study will be carried out in nursing homes in Flanders, the Dutch-speaking part of Belgium. Nursing homes are included if:
they have at least 100 bedsthe facility manager expresses explicit motivation to participate in the study and agrees to allocate 0.10 FTE per week for at least two staff members per 30 to 40 nursing home beds to act as ‘ACP Reference Person(s)’.

Nursing homes are excluded if:
they have taken or are taking part in another research study that is evaluating palliative care services or communication strategies, currently or in the past four yearsthey have developed - or are planning to develop during the foreseen duration of the trial - an extensive ACP policy, meaning that (i) all nursing home residents, or their families, regularly receive ACP conversations (two conversations or more each year) or (ii) the nursing home is judged by the researchers as having explicit and detailed ACP guidelines available (corresponding to high-quality ACP procedures and practices).major organisational or physical changes to the facility (e.g. building activities or staff re-organisation) are planned or ongoing during the study priodthey were involved in the development of the intervention programme.

### Study population and respondents

#### Nursing home staff and volunteers

Both the intervention and data collection methods are targeted at multiple staff members and volunteers working in the nursing home. Nursing home staff are people employed by the nursing home and include two groups:
nursing home ‘care’ staff are nurses, care assistants, psychologists, physiotherapists, occupational therapists, social workers, animators, pastoral or spiritual caregivers, moral consultants, reference persons for dementia or reference persons for palliative carenursing home ‘support’ staff are staff working in the nursing home but without having a role in care provision i.e. cleaning, administrative, technical/logistical or kitchen staff who have regular contact with residents or family but do not provide direct care to them.

Nursing home staff are included if they are able to speak and understand Dutch. Volunteers are included if they are registered at the nursing home and able to speak and understand Dutch. Students, interns or volunteers under 18 years old are excluded from participation.

#### Nursing home residents and family

The intervention will not be directly targeted at nursing home residents or family, as ACP+ is a training and support programme directed at nursing home staff level. As part of the process evaluation, we will conduct semi-structured interviews with a small sample of residents and their families from the intervention nursing homes who have participated in ACP conversations. Family members are defined as relatives or friends of the resident and identified by the nursing home care staff. People younger than 18 years, unable to understand or speak Dutch or unable to provide written informed consent are excluded from participation.

### Intervention: the ACP+ programme

The ACP+ programme is a multicomponent theory-based intervention aimed at training and supporting nursing home staff with the implementation of ACP into daily nursing home care and routine practice. It is focused around training and coaching, management buy-in, identifying roles and responsibilities in having ACP conversations with all residents and/or their families, documentation and information transfer, regular follow-up during multidisciplinary meetings and audit, and also includes possibilities of tailoring specific elements to the local context. The programme includes ten intervention components, 22 activities and 17 materials to support its delivery, detailed in Table 4 and Table 1. The components are to be implemented stepwise over the course of eight months, with the help of one or two external trainer(s) whose support decreases as the nursing home becomes more autonomous in organising ACP. These trainers understand that coaching and communication are important to change practice, they have clinical practice experience in nursing homes, experience in delivering palliative care, and in performing ACP conversations. Ultimately, a family physician and a nurse were selected.

**Table 1 Tab1:** Summary of the ACP+ programme using the Template for intervention description and replication (TIDieR) checklist [18]

TIDieR number*	TIDieR item	ACP+ intervention program
1	BRIEF NAME (name or a phrase that describes the intervention)	The intervention is called “The ACP+ programme” (Dutch: *“Het VZP*^*+*^ *programma”*) and has been developed to implement and improve advance care planning in routine care practice in nursing homes in Flanders, Belgium.
2	WHY (any rationale, theory, or goal of the elements essential to the intervention)	Research shows that only a minority of older people actively engage in ACP, and that there is still a low prevalence of ACP in Flemish nursing homes [6, 19]. Nonetheless, a majority of the growing population of older people would appreciate an opportunity for such discussions and planning [20, 21]. The overall aim of ACP is to improve quality of care, quality of life and quality of dying of residents in nursing homes in Flanders. The theoretical model which was developed in the first phase of intervention development additionally provides a rationale for the individual elements essential to the intervention. This Theory of Change map is reported elsewhere [10].
3	WHAT Materials (any physical or informational materials used in the intervention, including those provided to participants or used in intervention delivery or in training of intervention providers)	17 intervention materials are provided to support delivery of the ACP+ programme: 1. Manual for the ACP Trainer, highlighting key issues of the ACP+ programme and guidance for ACP Trainer to perform his/her tasks 2. Information guide for nursing home management, highlighting key issues and challenges of ACP, explaining ACP+, how it should be implemented, what everyone’s roles are and how they should carry out all the steps within the ACP+ programme 3. Tailoring checklist, including information per intervention activity about the minimum of elements that should be held constant over all nursing homes and which elements can be adapted to each nursing home routines 4. Training manual for two-day training of ACP Reference Persons including educational materials for the ACP Trainer to be used in training 5. ACP manual for ACP Reference Persons including all materials that can be used in the implementation and organization of all intervention activities of the ACP+ program 6. Summary list on which nursing home staff notes all residents and their loved ones, that are eligible for an ACP conversation. This list provides an overview of who scheduled a planned ACP conversation and when. 7. Invitation letter for residents and family, inviting them to participate in information session about ACP 8. ACP information brochure for residents and family 9. Invitation letter for GPs, inviting them to participate in information session about ACP 10. ACP iormation brochure for professionals 11. Training manual for ACP Reference Persons to train other nursing home staff 12. ACP Conversation Guide providing information about initiating and preparing ACP conversations. The guide is structured as follows: A) ideas about a good life and discussing broader views and values (e.g. “What makes your life meaningful?”); B) preferences for current care (“What makes you worry?”), C) the importance of ACP (“Have you ever thought about what kind of care you would want (or not) in case you would be too sick to tell it yourself?”); D) shared care goals (e.g. “Do you feel it is important to make your own decisions with regards to your care? What do you feel is more important: quality of life or living as long as possible, not matter what?”); E) surrogate decision-maker/representative (e.g. in case you were too sick to make your own decisions regarding care, who do you trust to make medical decisions instead?”); F) documenting preferences, including advance directives; G) Place of death; H) other preferences (e.g. “Do you have other wishes that we can take into account?”); I) wishes regarding death (e.g. “Do you prefer to have specific rituals?”); J) revising preferences (e.g. “Under which circumstance would you like to definitely revisit your wishes?”). The conversation guide starts by exploring the broader views of the person and wishes regarding? Current care, and subsequently focuses on future care and end of life and dying. 13. ACP Conversation Tool, a short A4 document that staff can use during ACP conversations. It includes probe questions and brief conversation guidelines following the same structure as the full conversation guide. 14. ACP Document to document outcomes of ACP conversation(s); that can also be used as a transfer document to accompany the resident when transferring between care settings (e.g. ICU). 15. Standardised advance directives 16. Guideline about ACP in dementia for professionals working with people living with dementia [22] 17. ACP audit instrument
4	WHAT Procedures (each of the procedures, activities, and/or processes used in the intervention, including any enabling or support activities)	The ACP+ programme entails 10 intervention components that can be carried out via 22 intervention activities: As part of ‘ACP Trainer’ component (1) Activity 1: Selection and preparation of two ACP (external) Trainers Activity 2: ‘Shadowing’. During the first four months, the trainer follows the selected ACP Reference Persons in their daily job to get familiar with the aspects related to the nursing home, certain routines and ACP-related activities that are already in place As part of ‘Buy-in management’ component (2) Activity 3: Meeting(s) between the ACP Trainer and the nursing home management, representatives of the board of directors, head nurses and the coordinating advisory physician† to explain the project and ask management for their (active) participation (including integrating ACP in the general policy of the nursing home and ensuring staff is able to spend time on their tasks to implement and organize the ACP+ programme and ACP in general, within the routine care). During this meeting they suggest nursing home staff eligible to function as ACP Reference Person‡ (in consultation with staff themselves) Activity 4: Follow-up meetings between management, other decision-makers, ACP Reference Persons and the ACP Trainer. As part of ‘tailoring’ component (3) Activity 5: Tailoring-meeting(s) between ACP Reference Persons, management and important decision-makers‡ about how to fit the implementation of the ACP+ programme to routines As part of ‘ACP Reference Persons’ component (4) Activity 6&7: Two-day interactive training (session 1 and 2) for the ACP Reference Persons Activity 8: Come-back seminar for all ACP Reference Persons As part of ‘information about ACP’ component (5) Activity 9: Information (session(s)) for all residents and their families about ACP in the nursing home during a format that is ‘tailored’ to routines in the specific nursing home setting (e.g. resident/family council, individually, exceptional information session) Activity 10: Information session(s) for all GPs about ACP in the nursing home, including motivating them to consider the wishes and preferences of their patients in (end-of-life) decision-making and to engage in ACP of their patients. GPs are invited to an information session after 5 p.m., accreditation can be arranged. As part of ‘in-house training’ component (6) Activity 11&12: In-house 2-h training sessions (session 1 & 2) to train ‘ACP Conversation Facilitators’ in performing ACP conversations Activity 13: In-house 1,5-h training session to train ‘ACP Antennas’ to educate them how to recognize triggers in residents and family, so they are more willing to have spontaneous ACP conversations according to their competencies and so they know how to pass on information to other staff As part of the ACP planned conversation(s) (7) Activity 14: Exploration of earlier wishes and GP involvement. Activity 15: First planned ACP conversation with resident and family Activity 16: ACP follow-up conversation(s) Activity 17: Documentation of wishes and preferences As part of ‘information transfer’ component (8) Activity 18: Integration of ACP into multidisciplinary meetings so information is shared across professionals in the nursing home As part of ‘coaching’ component (9) Activity 19: One-to-one coaching on request, by ACP Trainer to nursing home staff Activity 20: In-house specialization session 1 (at least 2 hrs): Dementia Activity 21: In-house specialization session 2 (at least 2 hrs): Communication with other healthcare professionals As part of ‘audit’ component (10) Activity 22: ACP audit meeting(s) to discuss ACP procedures with all involved healthcare professionals, the coordinating advisory physician and the management to identify problems and discuss action plans for improvement
5	WHO PROVIDED (intervention provider, their expertise, background and any specific training given)	- ACP Trainers will be available to support nursing homes in implementing ACP into routine care. These trainers are skilled and experienced in change management, have clinical practice experience in nursing homes and in performing ACP conversations. They are able to train other professionals. Their support decreases as nursing homes become more autonomous in organising ACP. - ‘ACP Reference Persons’ are professionals employed by the nursing home who have roles in daily resident care (e.g. head nurses, team coordinators, nurses, palliative care reference persons, reference persons for dementia, psychologists, members of the palliative (support or care) team/working group). The ACP Reference Persons’ main responsibility is to implement and sustain ACP within the nursing home. They market the program, communicate the high priority for nursing home residents, provide education (to ACP Conversation Facilitators and ACP Antennas), conduct ACP conversations with residents and/or family, and perform regular monitoring to audit advance care planning processes, structures and outcomes within the nursing home. - ‘ACP Conversation Facilitators’ or other (head) nurses, palliative care reference persons, reference persons for dementia, psychologists, social workers, care assistants, pastoral or spiritual caregivers, moral consultants and members of the palliative (support or care) team/working group that are willing. These trained conversation facilitators are - together with ACP Reference Persons - responsible for planning and performing regular *manualized* ACP conversations with residents and/or family. - ‘ACP Antennas’ are all others. This is usually staff that do not necessarily provide resident care but do have daily contact with residents and/or family (e.g. care assistants, hair dressers, cleaning staff, administrative staff, volunteers, ...). They will receive a short training in a much easier formulae in recognizing and signalling triggers that can signal the person is ready or willing to engage in ACP.
6	HOW (modes of delivery)	All intervention activities are provided face-to-face, individually, in duo or in groups with a maximum of 15 participants.
7	WHERE (the type(s) of location(s) where the intervention occurred, including any necessary infrastructure or relevant features)	The intervention is meant to improve ACP in nursing homes in Flanders (Belgium). These nursing homes are skilled nursing care facilities where older adults reside who have problems with activities of daily living and/or physical and cognitive functioning [23]. Most residents are still supervised by their GP but since 2000, each nursing home is legally obliged to have a coordinating advisory physician, a GP, preferably trained in gerontology whose tasks include among others, consultancy and conflict mediation in palliative care situations. In addition, nursing homes must cooperate with the geriatric service of the regional hospital and a specialized service of palliative care [24]. The two-day training for the ACP Reference Persons is organised across all nursing homes in a geographically central location. The other training and information sessions are organised in-house. ACP conversations or meetings can be held in a private room in the nursing home.
8	WHEN and HOW MUCH (the number of times the intervention was delivered and over what period of time including the number of sessions, their schedule, and their duration, intensity or dose)	ACP+ should be implemented over the course of 8 months and includes a thorough preparatory or training phase (month 1 to 4) and a follow-up phase (month (5 to 8). Information and training sessions vary from 1 h to two days, depending on the type. ACP conversations are known to vary between 60 and 240 min [25].
9	TAILORING (if the intervention was planned to be personalized, titrated or adapted, then describe what, why, when, and how)	To maximize the fit between individual nursing home needs and ACP+, participating nursing homes have the opportunity, in consultation with the trainer, to choose how they operationalize some activities (e.g. how to fit intervention activities into existing work schedules (e.g. training during lunch, information session for GPs in the evening), how activities are routinely discussed (formally and informally, e.g. through posters, meetings, family council), who needs to be involved in decision-making and how proposed materials can be entered into existing electronic systems).

*ACP* advance care planning; GP general practitioner

**TIDIER* items ‘modifications’ and ‘how well the intervention was implemented’ cannot be reported here and can only be described after the study is complete

†Nursing homes are legally obliged to have at least one coordinating and advisory physician (remunerated according to the number of beds), who coordinates medical care in the facility, as well as reference nurses for palliative care [26]

‡Decision-makers are considered to be: head of nursing staff, head of residents’ care, nursing home management. All those involved with decision-making tasks in the nursing home

A key aspect of the programme is the imparting of different roles in the nursing home: ‘ACP Reference Persons’ will be responsible for implementing ongoing ACP within the nursing home; ‘ACP Conversation Facilitators’ work with ACP Reference Persons and are responsible for planning and performing regular ACP conversations with residents and/or family; all other staff, including support staff (administrative, technical, cleaning staff) and volunteers, are ‘ACP Antennas’, who recognise and signal triggers that indicate a persons’ readiness, need or willingness to engage in ACP.

To develop the ACP+ programme, we first applied a Theory of Change approach to develop a theoretical model of all intermediate steps necessary to achieve desired long-term outcomes for nursing home residents and their families [10]. We constructed this model through 1) context analysis of facilitators/barriers that enhance or inhibit ACP, 2) systematic review of preconditions for ACP in nursing homes [8] and 3) two workshops with stakeholders to identify how ACP is expected to work in the local context in order to achieve its desired long-term outcomes [10]. We then operationalised key intervention components – identified as part of this theoretical model – into specific activities and materials, through expert discussions and review of existing ACP programmes, and we evaluated the programme (including the activities and materials) for perceived feasibility and acceptability of its implementation in nursing homes through interviews with nursing home management and staff of five nursing homes, and expert revisions; ethics approval was granted by the Ethics Committee of University Hospital Brussels (2017/31, (B.U.N. 143,201,732,133). A standardised description of the final ACP+ programme, according to the TIDieR checklist can be found in Table 1.

